### 2.5. Statistical Analysis Plan

Continuous variables will be presented as the mean and standard deviation or as the median and interquartile range. Normality in the distribution will be tested with the Shapiro–Wilk test. Categorical variables will be summarized in terms of absolute and relative frequencies.

To determine whether the new diagnostic protocol can improve the ability to detect hydrocephalus as well as the timeliness of the diagnosis and the clinical rehabilitative outcomes, the historical and prospective cohorts will be compared with respect to the following: hydrocephalus diagnosis detection rate, time from admission to diagnosis, LOS, incidence of clinical complications, and DRS and LCF scores at discharge (T3). In the subgroup of patients with low responsiveness, the clinical rehabilitative outcome at discharge will be measured using the CRS-R score. Continuous variables will be compared using Student’s *t* test, when normally distributed, or the Mann–Whitney U test otherwise. Categorical variables will be compared using Pearson’s χ^2^ test or Fisher’s exact test as appropriate. The same tests will be used to compare patients with and patients without a diagnosis of hydrocephalus belonging to the prospective cohort, in terms of the following: clinical rehabilitative outcome at T3 and T4 measured using the DRS, LCF and CRS-R scale scores; evolution from T0 to T4 of quality of life measured using the QOLIBRI-OS; neuroradiological characteristics at T1 and T3 or T4 measured using Evan’s index, callosal angle and volumetric analysis. To complement the information provided by the statistical tests, differences between groups will be quantified in terms of the effect size (standardized mean differences for continuous variables; difference between proportions or odds ratios for categorical variables) and its standard error. In addition, outcome variables will be compared between the historical and prospective cohorts, adjusting for demographic and clinical confounders in multivariable regression analyses. Confounders to be included in the models are those significantly associated with the outcomes and significantly different between the two cohorts. 

Two-sided tests will be carried out, and the statistical significance level will be set at 0.05. All analyses will be performed with Stata version 17.0 (Stata Corp., College Station, TX, USA).

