## 3. Expected Results

We expect to find, in the prospective cohort as compared to the historical cohort, an increase in the proportion of diagnosed cases, a significant reduction in the time elapsed between admission and diagnosis and, consequently, a shortened time to surgery as well as a shortened overall LOS.

We assume that early diagnosis and treatment may result in a decreased incidence of clinical complications and may improve the rehabilitative outcomes at discharge among patients with hydrocephalus, especially in the subgroup with low responsiveness.

In addition, we expect to obtain useful information about the diagnostic and prognostic value of the neuroradiological characteristics.

Lastly, from the comparison of patients with and without hydrocephalus in the prospective cohort, we expect to observe that the adoption of an objective and timely protocol for the diagnosis and treatment will allow patients with hydrocephalus to obtain similar clinical rehabilitative outcomes and perceived quality of life to those who do not develop this complication.

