**Figure 2 brainsci-13-01067-f002:**
[figure not shown]
Study flow-chart.

**Table 1 brainsci-13-01067-t001:** Clinical parameters, scales and exams of the study.

Type of Evaluation	
Clinical parameters	- Neurological status - Presence of tracheostomy or mechanical ventilation - Feeding - Dysphagia - Sensory deficits - Cognitive and behavioral deficits - Clinical complications
Clinical measurement scales	- Glasgow Coma Scale (GCS) [21] - Disability Rating Scale (DRS) [22,23,24] - Levels of Cognitive Functioning (LCF) [24,25,26,27] - Coma Recovery Scale Revised (CRS-R) [28,29,30] - MiniMental State Evaluation (MMSE) [31,32] - Montreal Cognitive Assessment (MoCA) [33] - Modified Ashworth Scale (MAS) [34] - Modified Barthel Index (MBI) [35,36,37] - Glasgow Outcome Scale (GOS) [38] - Quality of Life after Brain Injury Overall Scale (QOLIBRI-OS) [39,40]
Functional tests	- Timed “Up-and-Go” test (TUG) [41] - 10 m Walking Test (10 mWT) [42] - Tinetti Performance Oriented Mobility Assessment (POMA) [43]
Neurophysiological exams	- Electroencephalograph EEG - Event-related brain potential (p300/ERB) - Somatosensory-evoked potentials to upper limb (SEPs)
Neuroradiological exams	- Brain CT scan - Brain 3T MRI

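### The covariate rule for the historical-versus-prospective models has no time limit, so it permits adjustment for consequences of the diagnostic protocol

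*Protocol article*

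**What the plan says.** Section 2.5 first compares the two cohorts without adjustment on "hydrocephalus diagnosis detection rate, time from admission to diagnosis, LOS, incidence of clinical complications, and DRS and LCF scores at discharge (T3"). It then adds models "adjusting for demographic and clinical confounders in multivariable regression analyses" and gives the entry rule: "Confounders to be included in the models are those significantly associated with the outcomes and significantly different between the two cohorts". The only significance level stated is in the same section: "Two-sided tests will be carried out, and the statistical significance level will be set at 0.05". Section 2.5 gives no candidate list and does not say when a candidate must have been measured. Section 2.4 does define a baseline, T0, as the first 7 days after admission, but 2.5 does not refer to it here.

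Two other places bear on which variables could pass. Table 1 lists complications among the clinical parameters ("Cognitive and behavioral deficits - Clinical complications"). Section 3 expects "an increase in the proportion of diagnosed cases, a significant reduction in the time elapsed between admission and diagnosis", followed by shorter time to surgery and shorter stay, and adds: "We assume that early diagnosis and treatment may result in a decreased incidence of clinical complications and may improve the rehabilitative outcomes at discharge".

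**The concern.** The two criteria are association with the outcome and difference between cohorts. A true confounder meets both, but so does a variable that the protocol changes and that in turn affects the outcome. Significance tests cannot tell the two apart. Section 3 describes such a path: the protocol brings earlier diagnosis and surgery, then fewer complications, and with them shorter stay and better discharge scores. If that expectation is right, the intermediate steps tend to meet the rule.

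A model that adjusts for an intermediate step estimates only the part of the effect that bypasses it. This matters because the control group is historical and not randomised. The crude comparison is open to differences in case mix, so readers will lean on the adjusted result.

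**Working it through.** **Inputs from the article.** Recruitment is 50–60 patients a year for two years, with about 20% having hydrocephalus (section 2.2). This reproduces the stated feasibility figure: 2 × 50 to 2 × 60 = 100–120 patients, and 0.20 × 100 to 0.20 × 120 = 20–24 cases. The introduction cites 13.2% of 621 patients from an earlier study. The historical window is 2015–2019 (section 2.1), but its size is not given.

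**Assumptions.** Historical cohort: 5 × 50 to 5 × 60 = 250–300, taken as 275, with 621 as an upper case. Prospective cohort: 110. Each complication adds 30 days to the stay, 5 days are saved by other routes, and the residual SD is 50 days. None of the complication or length-of-stay figures is in the article.

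**1. How large a fall in complications is plausible?** Section 3 places the benefit among patients with hydrocephalus, about 20% of the cohort. If only they benefit, a fall of d points across the cohort needs d / 0.20 points among them:
- 40% to 35%: 5 / 0.20 = 25 points.
- 40% to 32%: 8 / 0.20 = 40 points. If these patients share the 40% rate, this abolishes all their complications.
- 40% to 25%: 15 / 0.20 = 75 points.
- 50% to 30%: 20 / 0.20 = 100 points.

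The last two exceed what a shared 40% or 50% rate allows.

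**2. What the rule does with complications (simulation).** The variable enters if its chi-square test between cohorts and its t test against length of stay both give p < 0.05. True saving = 30 × fall + 5 days. Once the variable is in the model, the estimate centres on the 5 days that bypass it.

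| Fall in complications | True saving (days) | Enters in | Mean saving under the rule (days) |
|---|---|---|---|
| 40% to 35% | 30 × 0.05 + 5 = 6.5 | about 15% | about 6.0 |
| 40% to 32% | 30 × 0.08 + 5 = 7.4 | about 30% | about 6.1 |
| 40% to 25% | 30 × 0.15 + 5 = 9.5 | about 81% | about 5 where it enters |
| 50% to 30% (300 v 120) | 30 × 0.20 + 5 = 11 | about 97% | about 5 where it enters |

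Across repeated runs, the first two rows give entry of about 14–32% and a mean loss of about 0.5–1.4 days. If the analysis covers diagnosed patients only (about 0.132 × 275 = 36 v 0.20 × 110 = 22), 40% to 25% gives entry in about 13% and a mean of 7.9 days against 9.5. A fall of 50% to 30% gives about 21%, and 8.2 days against 11.0.

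**3. Diagnosis as a covariate.** At 13.2% v 20%, the cohort-difference test alone is passed with probability 37–42% (250–300 historical patients) or 45–50% (621). Adjusted minus unadjusted effect = −b × (0.20 − 0.132) = −0.068b, where b is the outcome difference between diagnosed and undiagnosed patients. If diagnosed patients have worse (higher) DRS scores, b > 0 and adjustment makes the protocol look better. If b < 0, it looks worse.

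**4. Time to diagnosis.** It exists only for diagnosed patients, so it cannot enter an all-patient model. It could enter a model of diagnosed patients, the group for which the introduction states the aims on stay and complications. With 33 v 20 to 40 v 24 patients (13.2% of 250–300; 20% of 100–120), an assumed shortening of 0.8 SD and a correlation of 0.4–0.6 with length of stay, it enters in about 72–86% of studies. If the whole effect runs through it, the mean estimate falls from 0.31–0.49 SD to 0.03–0.05 SD. With a 0.5 SD shortening, entry is about 37–47%.

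**5. With candidates limited to T0.** None of these variables can enter, and the adjustment no longer removes any part of the protocol's effect.

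**The case against.** The strongest reply is that the article never proposes these covariates. It speaks of confounders, a word that in ordinary use excludes consequences of the intervention, and it gives detection, time to diagnosis, stay and complications the role of outcomes. The selection sentence can be read as a filter on variables already judged to be confounders. Table 1 lists every evaluation and assigns no analysis role. A condensed article may also leave the candidate list to a fuller plan.

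Much of this stands: the rule permits the error and does not prescribe it. What it does not answer is that the article states an operative selection rule, and a later plan that follows it literally inherits the gap. Being an outcome in one model does not bar a variable from another.

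A reader might go further and infer that these variables enter exactly when the protocol works, and that adjustment then removes the effect. The documents do not support that. At the article's own 20%, set against 13.2%, diagnosis passes the cohort test in at most about half of studies. Only the share of the effect acting through the variable is lost, and adjusting for diagnosis need not bias towards no benefit. Losing about half of the saving requires a cohort-wide fall in complications that is hard to square with benefit in about 20% of patients. Finally, the adjusted models are additional, so a shrunken estimate would be visible beside the crude one.

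**Conclusion.** The point holds as a minor one. The rule in 2.5 has no time limit and cannot separate confounders from consequences of the protocol, and it admits a consequence more often the more the protocol changes it. Under the more plausible falls in complications (40% to 32–35%), the average cost is about 0.5–1.4 days out of roughly 6.4–7.4. It could be larger for time to diagnosis among diagnosed patients if that variable carried the whole effect. These figures rest on assumed complication rates, effects, correlations and historical cohort size, so they show direction and order of size only. The unadjusted comparisons are unaffected, but with a historical control the adjusted models matter most for the conclusion.

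**What to change.** In section 2.5, restrict the candidate covariates for all historical-versus-prospective models to a pre-specified list of variables fixed at or before T0: demographics, aetiology, injury characteristics and clinical status at admission. State that hydrocephalus diagnosis, time to diagnosis, tap test, shunt placement, complications and length of stay are not used as covariates in these models. This takes a sentence or two and no new data. It is best done before the cohorts are compared.

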## 3. Expected Results

We expect to find, in the prospective cohort as compared to the historical cohort, an increase in the proportion of diagnosed cases, a significant reduction in the time elapsed between admission and diagnosis and, consequently, a shortened time to surgery as well as a shortened overall LOS.

We assume that early diagnosis and treatment may result in a decreased incidence of clinical complications and may improve the rehabilitative outcomes at discharge among patients with hydrocephalus, especially in the subgroup with low responsiveness.

In addition, we expect to obtain useful information about the diagnostic and prognostic value of the neuroradiological characteristics.

Lastly, from the comparison of patients with and without hydrocephalus in the prospective cohort, we expect to observe that the adoption of an objective and timely protocol for the diagnosis and treatment will allow patients with hydrocephalus to obtain similar clinical rehabilitative outcomes and perceived quality of life to those who do not develop this complication.

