## 2. Materials and Methods

### 2.1. Study Design, Setting and Population

The protocol will be applied to a prospective cohort recruited in a tertiary referral rehabilitation center in Italy, highly specialized in sABIs. Patients aged 18 or older with a diagnosis of an sABI of any etiology will be eligible for the study. Exclusion criteria are as follows: diagnosis and/or treatment of hydrocephalus prior to hospital admission at our institution; presence of acute hydrocephalus; pre-existing neurological or psychiatric comorbidities. 

Patients with and without a diagnosis of hydrocephalus in this prospective cohort will be compared in terms of clinical rehabilitative outcomes, the evolution of quality of life and neuroradiological characteristics.

A historical cohort will serve as a control group and will include all hospitalized patients with sABIs between 1 January 2015 and 31 December 2019. The years 2020 and 2021 will be excluded in order to avoid selection bias due to the organizational measures taken to counteract the impact of the SARS-CoV-2 pandemic. 

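### Similar outcomes in patients with and without hydrocephalus are credited to adopting the protocol, but the comparison lies wholly inside the cohort managed under it and cannot show what adoption changed

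*Protocol article*

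**What the plan says.** The last paragraph of section 3 (Expected Results) names the evidence and the conclusion in one sentence. The evidence comes "from the comparison of patients with and without hydrocephalus in the prospective cohort". The conclusion is about adoption: "we expect to observe that the adoption of an objective and timely protocol for the diagnosis and treatment will allow patients with hydrocephalus to obtain" outcomes and perceived quality of life like those of patients who do not develop hydrocephalus.

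Section 2.5 plans the matching test: "The same tests will be used to compare patients with and patients without a diagnosis of hydrocephalus belonging to the prospective cohort". The outcomes are DRS, LCF and CRS-R at T3 and T4, neuroradiological measures, and "evolution from T0 to T4 of quality of life measured using the QOLIBRI-OS".

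A pre-protocol comparator exists. Section 2.1 states: "A historical cohort will serve as a control group and will include all hospitalized patients with sABIs between 1 January 2015 and 31 December 2019". Section 2.5 compares the two cohorts on "hydrocephalus diagnosis detection rate, time from admission to diagnosis, LOS, incidence of clinical complications, and DRS and LCF scores at discharge (T3"), with CRS-R at discharge in patients with low responsiveness. It adds that "outcome variables will be compared between the historical and prospective cohorts, adjusting for demographic and clinical confounders in multivariable regression analyses". For the discharge scores, neither the unadjusted nor the adjusted comparison is described as split by hydrocephalus status. Neither T4 nor QOLIBRI-OS is among the outcomes listed for the cohort comparison.

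**The concern.** A statement about what adoption achieved needs a contrast between adoption and non-adoption. Inside the prospective cohort adoption does not vary. If patients with hydrocephalus do about as well as the others there, this may be because the protocol closed a gap, or because there was little gap before it. The Introduction makes the second possibility credible: in the earlier study, most shunted patients improved and none worsened. In the other direction, a large earlier gap could have narrowed substantially and still be visible in the prospective cohort.

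At stake is one interpretive conclusion. It matters because section 5 links the protocol's usefulness to its uptake by other centers. The main comparison of the two cohorts is not affected.

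**Working it through.** **1. The logic.** Let g1 be the with-versus-without gap in the prospective cohort and g0 the same gap in 2015–2019. What adoption is said to have done to the gap concerns g1 − g0. The plan estimates g1 only. Any value of g1, including zero, is compatible with g1 − g0 being negative, zero or positive. A perfect equivalence result for g1 would not change this.

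**2. The plan's own figures.** Section 2.2 gives two years at 50–60 patients per year and about 20% with hydrocephalus.
- 2 × 50 = 100 and 2 × 60 = 120 patients.
- 20% of these is 20 and 24, leaving 80 and 96 without hydrocephalus.

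This reproduces the stated 100–120 patients with at least 20 cases.

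**3. Precision of g1 in SD units.** SE = √(1/n₁ + 1/n₂).
- 20 v 80: √(0.0500 + 0.0125) = 0.250; 95% half-width 1.96 × 0.250 = 0.49.
- 24 v 96: √(0.0417 + 0.0104) = 0.228; half-width 0.45.

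**4. Precision of g1 − g0.** The article does not give the size of the historical cohort. Assume 5 years at 50–60 per year, so 250–300 patients, with the 13.2% incidence that the Introduction reports from a previous study of 621 patients. That gives 33 v 217, or 39.6 v 260.4. The SE is the square root of the sum of the four 1/n terms.
- 250 historical with 20 v 80: √(0.0303 + 0.0046 + 0.0625) = 0.312; half-width 0.61.
- 300 historical with 24 v 96: √(0.0253 + 0.0038 + 0.0521) = 0.285; half-width 0.56.

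The change detectable with 80% power at two-sided 0.05 is 2.80 × SE, about 0.87 and 0.80 SD. However large the historical cohort, the half-width cannot fall below the 0.49 and 0.45 SD of step 3.

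**5. Can the gap change with no true effect?** Diagnosis is reached differently in the two periods (Introduction against section 2.4), and the diagnosed share is expected to rise from 13.2% to about 20%. For illustration, assume true prevalence 20% in both periods, 13.2% detected before and all detected after, nobody's outcome altered, and the cases detected before 0.8 SD worse than non-cases. The missed 6.8% sit in the comparison group before and in the diagnosed group after.

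| Missed cases worse by | Gap before | Gap after |
|---|---|---|
| 0.2 SD | 0.8 − (6.8 × 0.2)/86.8 = 0.78 | (13.2 × 0.8 + 6.8 × 0.2)/20 = 0.60 |
| 1.2 SD | 0.8 − (6.8 × 1.2)/86.8 = 0.71 | (13.2 × 0.8 + 6.8 × 1.2)/20 = 0.94 |

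The gap appears to narrow in the first row and to widen in the second, though the protocol does nothing to outcomes in either. The SD values are illustrative. The second row reflects the article's own suspicion that cases were missed especially in patients with disorders of consciousness.

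**The case against.** The strongest reply is that section 2.5 already sends the protocol-effect question to the right place. It introduces the historical-versus-prospective comparison as the means of judging whether the protocol improves detection, timeliness and rehabilitative outcomes. It does not present the with-versus-without comparison as a test of the protocol, and section 2.1 describes that comparison neutrally. Similarity to patients without hydrocephalus is not one of the four aims in the Introduction. This stands, and it confines the fault to the conclusion drawn in section 3. It does not remove the fault, because that sentence ties the conclusion to the within-cohort comparison by name.

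A reader might infer three stronger things that the documents do not support.

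- *That the study has no pre-protocol control, or never uses it by diagnosis.* It has one. Time from admission to diagnosis, a planned between-cohort outcome, exists only for diagnosed patients. The fourth aim concerns patients diagnosed and treated, and section 3 expects better discharge outcomes among those with hydrocephalus. What is not planned is a historical with-versus-without gap.
- *That the chance of a non-significant result measures the problem.* Under the rule "Two-sided tests will be carried out, and the statistical significance level will be set at 0.05", a small true gap in 20 v 80 patients would often be missed. That concerns using a difference test to claim similarity, which is a separate matter. The article also states no rule that reads non-significance as a protocol effect, and it commits to effect sizes with standard errors.
- *That a cohort-by-hydrocephalus interaction would supply the causal answer.* Steps 4 and 5 show that it would be imprecise and could move through relabelling alone.

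**Conclusion.** The point holds in a limited form. The attribution in section 3 does not follow from the comparison it cites, and this would be so even if the plan were carried out exactly. That conclusion rests on the wording of sections 2.1, 2.5 and 3 and on no assumed number.

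Its reach is one interpretive claim covering T3, T4 and QOLIBRI-OS. For T4 and QOLIBRI-OS the listed between-cohort outcomes offer no alternative, so those results can only describe the prospective cohort. For T3 DRS and LCF a historical gap could be estimated as context. The change in the gap would carry a 95% CI of about ±0.56 to 0.61 SD under the assumed 250–300 historical patients and 13.2% diagnosed, and it would be open to the shift in who is diagnosed.

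**What to change.** 1. In section 3, state that the with-versus-without results at T3, at T4 and for QOLIBRI-OS describe the prospective cohort and are not evidence of a protocol effect. Rest statements about the protocol's effect on the historical-versus-prospective comparison already planned in section 2.5.
2. As a supportive analysis in section 2.5, report the with-versus-without difference in T3 DRS and LCF in the historical cohort beside the prospective one. Give the change in the gap with its 95% CI, adjusted for age, and for T0 score where it is available.
3. State with that analysis that the change in the gap is imprecise, that it can arise purely from the different diagnosed share in the two periods, and that it is not to be read as the causal effect of the protocol.

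Item 1 costs one reworded paragraph. Item 2 costs one model on T3 scores that the plan already takes from the historical cohort. Adjustment for T0 score may not be possible throughout: section 2.5 names only discharge scores for the historical comparison, and section 4 warns that historical data may be incomplete. If those data prove inadequate, item 1 alone resolves the point.

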### 2.2. Feasibility 

Patients with sABIs of different etiologies (traumatic, vascular, anoxic, infectious, neoplastic, etc.) will be recruited from those hospitalized in the Severe Acquired Brain Injury Unit or in the Intensive Care Unit (ICU), depending on their clinical conditions. The presence of an ICU in our rehabilitation institute ensures prompt treatment soon after the acute brain injury event, through the implementation of a personalized rehabilitation project in the early stage.

The recruitment of the prospective cohort will last two years. The expected annual flow of patients with sABIs is 50–60, and the expected proportion with hydrocephalus is about 20%, leading to a total number of 100–120 patients with sABIs and at least 20 patients with a confirmed diagnosis of hydrocephalus.

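### Patients with hydrocephalus are expected to do as well as those without, but the comparison is analysed only with tests of difference and no criterion for similarity, in about 20 v 80 to 24 v 96 patients

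*Protocol article*

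**What the plan says.** Section 3 (Expected Results) closes with an expectation about the prospective cohort alone: an objective and timely pathway "will allow patients with hydrocephalus to obtain similar clinical rehabilitative outcomes and perceived quality of life to those who do not develop this complication".

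Section 2.5 (Statistical Analysis Plan) assigns the analysis: "The same tests will be used to compare patients with and patients without a diagnosis of hydrocephalus belonging to the prospective cohort". The tests meant are Student's t for continuous variables "when normally distributed, or the Mann–Whitney U test otherwise", and Pearson's chi-squared or Fisher's exact test for categorical ones. The outcomes are DRS, LCF and CRS-R scores at T3 and T4, the T0–T4 course of QOLIBRI-OS, and neuroradiological measures. The decision level is common to all: "Two-sided tests will be carried out, and the statistical significance level will be set at 0.05".

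The same section adds standardized mean differences, differences in proportions or odds ratios, each with a standard error, as a complement to the tests. It gives no margin, and no rule for when two groups count as similar. Multivariable adjustment is described only for the historical v prospective comparison.

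Section 2.2 (Feasibility) gives the size: "The recruitment of the prospective cohort will last two years", "leading to a total number of 100–120 patients with sABIs and at least 20 patients with a confirmed diagnosis of hydrocephalus".

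**The concern.** The expectation and the analysis point in opposite directions. The expectation is that two groups do not differ by much. The tests take no difference as the null hypothesis, so the only positive finding that they can deliver is that the groups do differ. A large p-value leaves open whether the groups are alike or the sample was too small to tell.

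The incentive also runs the wrong way. Fewer confirmed cases, or more loss before the one-year visit, make a non-significant result more likely, and so make the hoped-for finding easier to reach. What is at stake is a statement that timely diagnosis removes the disadvantage of hydrocephalus. The Conclusions section foresees adoption by other centers and input to guidelines, so such a statement should rest on evidence for it.

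**Working it through.** **1. Group sizes (section 2.2).** 2 years × 50–60 per year = 100–120 patients. 20% of these = 20–24 with hydrocephalus. This reproduces the article's figures. The groups compared are therefore 20 v 80 to 24 v 96.

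**2. Standard error of a difference, in SD units.** SE = √(1/n₁ + 1/n₂).
- 20 v 80: √(0.0500 + 0.0125) = 0.250
- 24 v 96: √(0.0417 + 0.0104) = 0.228

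**3. Width of the 95% CI.** Half-width = t(0.975; n₁+n₂−2) × SE.
- 20 v 80: 1.984 × 0.250 = 0.50 SD
- 24 v 96: 1.980 × 0.228 = 0.45 SD

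At 20 v 80, even an observed difference of exactly zero would barely exclude a half-SD deficit.

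**4. Power of the planned test for one outcome** (two-sided 0.05, noncentral t with noncentrality d/SE). The article states no effect size, so d is an assumption and a range is shown.

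| True deficit | 20 v 80 | 24 v 96 |
|---|---|---|
| 0.3 SD | 22% | 26% |
| 0.5 SD | 51% | 58% |
| 0.7 SD | 79% | 86% |
| 0.8 SD | 89% | 94% |

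A true 0.5 SD deficit is missed 49% or 42% of the time. With the Mann–Whitney test on normal data (simulation, 10,000 runs) power is 49% or 56%, so the miss rate is 51% or 44%. The difference detectable with 80% power is (1.96 + 0.84) × SE = 0.70 SD or 0.64 SD.

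**5. Loss by T4.** If 20% were lost (assumed; 16 v 64), power for 0.5 SD falls to 42% and the half-width grows to 0.56 SD.

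**6. What a formal similarity claim could achieve.** Take an illustrative margin of 0.5 SD and no true difference.
- No worse outcome, one-sided 0.025 (one limit of the 95% CI): power = Φ(0.5/SE − 1.96) = 52% at 20 v 80 and 59% at 24 v 96. Reaching 80% needs about 40 with and 157 without hydrocephalus.
- Equivalence by two one-sided tests at 0.05 (90% CI inside the margin): power = 2Φ(0.5/SE − 1.645) − 1 = 28% and 42%.
- Equivalence with the whole 95% CI inside the margin: 2Φ(0.5/SE − 1.96) − 1 = 3% and 18%.

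So 20–24 cases can meet only wide margins.

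**The case against.** **No rule equating p>0.05 with similarity is written down.** This stands. A reader might infer that a non-significant result will be read as similarity, or that there is a 49% chance of declaring similarity falsely. The article says neither. What it leaves open is the criterion: the only formal threshold in section 2.5 is significance at 0.05.

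**Effect sizes with standard errors are planned, and a confidence interval follows from them.** True, and this softens the problem. It does not remove it, because nothing ties the interval to the word similar and there is no margin to judge it against.

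**A clear deficit would usually be found.** A reader might infer that non-significance is the likely result even if patients with hydrocephalus do clearly worse. The power table contradicts that: at 0.5 SD the chance of significance is already slightly above one half with the t test, and at 0.8 SD it is 89–94%. Non-significance is the likely result only for smaller deficits.

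**The miss rate is for one test, whereas the expectation covers several outcomes.** Fair. If the same 0.5 SD deficit applied to three outcomes correlated at 0.5–0.8 (assumed), simulation puts the chance that all three are missed at about 24–34% for 20 v 80 and 18–27% for 24 v 96.

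**This is not a main aim.** Correct. Similarity is not among the four aims in the Introduction, nor in the abstract's expected results, and the historical v prospective comparison is unaffected. This limits the severity.

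**A condensed article may leave a margin to the full plan.** This would excuse silence on a margin. It does not excuse naming tests of difference for an expectation of similarity, since both are stated in the article.

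**Conclusion.** The concern holds as a moderate point: the expectation of similar outcomes is paired with tests that cannot support it, and no margin or interval criterion is set. At the planned size, one test would miss a true 0.5 SD deficit 42–49% of the time (t test), and the 95% CI half-width is about 0.45–0.50 SD.

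These figures assume approximately normal outcomes with equal SDs, the 20% hydrocephalus proportion in section 2.2, and complete follow-up. The 0.5 SD benchmark is illustrative. The mismatch itself depends on none of these. CRS-R comparisons will be weaker still if the scale is used only in patients with low responsiveness, as section 2.4 indicates.

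**What to change.** In sections 2.5 and 3, state that patients with and without hydrocephalus will be compared by an estimated difference with its 95% CI, and that a non-significant test will not be interpreted as similarity. Reword the closing expectation in section 3 to match. This is a change of wording only; the planned effect sizes and standard errors already supply what is needed.

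If the similarity claim is to be kept:
- The clinical team should set a margin in scale points for DRS, LCF and QOLIBRI-OS before data are seen.
- The plan should say whether the claim is equivalence or no worse outcome, and at which interval level it is judged.
- The claim should be made only if the interval excludes the margin, and the result should otherwise be called inconclusive.
- The plan should note that 20–24 cases can meet only wide margins.

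An adjusted difference should not be required without more detail, because section 2.5 defines no adjustment model for this comparison.

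The cost is that the similarity claim becomes harder to make.
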